## Assignment of interventions: blinding

### Who will be blinded {17a}

Due to the nature of the intervention, this study will not be blinded. The researcher administering the intervention and the patients will be aware of their group assignments, as participation in the intervention requires awareness of the assigned group. Therefore, concealment of allocation is not feasible, and the study is designed as an open-label trial.

### Procedure for unblinding if needed {17b}

Blinding is not applicable in this trial; therefore, unblinding procedures are not required.

## Data collection and management

### Plans for assessment and collection of outcomes {18a}

In this study, data will be collected using a four-part questionnaire, as described below:Demographic and Clinical Information Questionnaire: This section gathers information on variables such as age, gender, educational level, occupation, marital status, income level, support resources, history of physical and mental illnesses, duration of PD, medications used, and family history of PD.Parkinson’s Disease Fatigue Scale Questionnaire: In this study, the PFS-16 will be used to assess fatigue levels in patients with PD. This questionnaire was developed in 2005 by Brown et al. in the UK to evaluate the impact of fatigue on daily life activities in these patients [42]. The PFS-16 consists of 16 items**,** with 7 questions assessing the experience and physical impact of fatigue**,** while the remaining 9 questions evaluate the effect of fatigue on daily activities and performance**.** Participants are required to respond based on their fatigue experiences over the past 2 weeks. Responses are rated on a Likert scale with the following options: strongly disagree [1], disagree [2], neutral [3], agree [4], and strongly agree [5]. A total score of 8 or higher indicates the presence of significant fatigue.General Self-Efficacy Questionnaire: In this study, the GSE-17 will be used to assess self-efficacy levels in patients with PD. This questionnaire was developed in 1982 by Sherer et al. to determine various levels of general self-efficacy. Sherer and Maddux suggested that, regardless of the individual items, this scale consists of three main factors**:** the willingness to initiate behavior, the willingness to extend effort to complete a task, and perseverance in overcoming obstacles [43]. The scale consists of 17 items, rated on a 5-point Likert scale from 1 to 5. Specifically, in items 1, 3, 8, 9, 13, and 15, a response of “Strongly Agree” is scored as 5, while “Strongly Disagree” is scored as 1**.** In the remaining items, the scoring is reversed. The maximum possible score is 85, while the minimum is 17. A higher score indicates a greater sense of self-efficacy. Scores ranging from 17 to 34 indicate low self-efficacy, 34 to 51 indicate moderate self-efficacy, and 51 to 85 indicate high self-efficacy**.**Short Form Parkinson’s Disease Quality of Life Questionnaire: In this study, the PDQ-8 will be used to assess the QOL in patients with PD. This questionnaire was developed in 1997 by Jenkinson et al. with the aim of providing a shorter and more efficient method for measuring the QOL in PD patients, thereby improving ease of use in clinical settings. The PDQ-8 is a shortened version of the 39-item Parkinson’s Disease Questionnaire (PDQ-39). The PDQ-39 consists of 8 domains, and the PDQ-8 is derived by selecting one question from each domain of the PDQ-39. These eight questions were chosen based on their ability to reflect the most important aspects of QOL related to PD [44]. This questionnaire consists of 8 questions, each with response options ranging from never (score 0) to always (score 4), using a Likert scale. The total score is calculated by summing the scores of each question. A higher score indicates poorer QOL.

### Plans to promote participant retention and complete follow-up {18b}

Participants will receive weekly text reminders and follow-up calls to support adherence. Attendance and completion of required tasks will be monitored, and missed sessions will be rescheduled when possible.

Participants who discontinue the intervention or deviate from the protocol will not be followed for outcome data, unless they voluntarily request to receive the study results or the educational care materials. In such cases, these materials will be provided, but no further data will be collected for analysis.

### Data management {19}

Data will be collected using paper-based questionnaires completed by participants. Responses will be entered into a password-protected laptop by the researcher. Each participant will be assigned a unique code, and no names or personal identifiers will be stored. As the data consist of numerical values only, no advanced security measures are applied. Data quality will be ensured through careful data entry and periodic checks for completeness and consistency.

### Confidentiality {27}

Personal information about participants will be collected using paper-based forms and assigned unique codes to ensure anonymity. Data will be stored securely on a password-protected laptop, and only the research team will have access to the information. Participant names and identifying details will not be recorded or shared with any external parties. After the study, data will be securely stored for future reference or analysis, or destroyed, depending on the study’s requirements. All efforts will be made to protect participant confidentiality before, during, and after the trial.

*Plans for collection, laboratory evaluation*,* and storage of biological specimens for genetic or molecular analysis in this trial/future use {33}.*

No biological specimens will be collected for genetic or molecular analysis in this trial. As a result, there are no plans for the collection, laboratory evaluation, or storage of such specimens.

## Statistical methods

### Statistical methods for primary and secondary outcomes {20a}

For data analysis, descriptive statistics, including mean and standard deviation, will first be calculated. In inferential statistics, to compare changes in the three quantitative variables across three time points (before the intervention, immediately after the intervention, and 1 month later) between the control and intervention groups, repeated measures analysis of covariance (ANCOVA) will be used, controlling for covariates. The Kolmogorov–Smirnov test will be applied to assess data normality, while Levene’s test will be used to examine variance homogeneity. All analyses will be performed using SPSS software, version 25.

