### Outcomes {12}

The primary outcome is quality of life, measured using the PDQ-8, at 1 month post-intervention to assess sustained effects. Secondary outcomes include fatigue (PFS-16) and self-efficacy (GSE-17), assessed at baseline, immediately post-intervention, and 1 month post-intervention. Data collection will be coordinated via telephone, and participants will be asked to visit the Isfahan Parkinson’s Charity Association to complete the questionnaires. If a participant is unable to attend, the researcher will complete the questionnaire at the participant’s residence.

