### Participant timeline {13}

#### Sample size {14}

To determine the sample size, assuming a normal distribution of quality-of-life data, the following formula will be used.$$n= \frac{2 \times {\sigma }^{2}{ \times ({Z}_{1-\beta }+ {Z}_{1-\alpha /2})}^{2}}{{({\mu }_{1}-{\mu }_{2} )}^{2}}$$

The standard deviation in the study by Moghtaderi et al. was reported to be approximately 6 [41]. Therefore, with a power of 80% (1 − β = 80%) and assuming a confidence level of *α* = 0.05, the required sample size for each group to detect a difference of 4 units (μ₁ − μ₂ = 4) is:$$n=\frac{2 \times {6}^{2} \times {(0.84+ 1.96)}^{2}}{{(4)}^{2}}=35.28\approx 36$$

The required sample size for each group will be 36 participants, resulting in a total of 72 samples. Considering a 10% dropout rate, a total of 80 participants will be required for the study.

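### The primary outcome is PDQ-8 at 1 month, but the only stated analysis compares changes over three time points and never names the 1-month between-group contrast as the primary test

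*Protocol article*

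**What the plan says.** Outcomes {12} fixes one scale and one visit: "The primary outcome is quality of life, measured using the PDQ-8, at 1 month post-intervention to assess sustained effects". Fatigue and self-efficacy are secondary.

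Sample size {14} uses the textbook formula for two independent means, "assuming a normal distribution of quality-of-life data, the following formula will be used", with an SD that "was reported to be approximately 6", 80% power, two-sided 5% and a target difference of 4 units. It has no term for repeated measures, correlation or covariates, and it names no visit.

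Statistical methods {20a}, which is headed as covering primary and secondary outcomes, gives one inferential method. Its purpose is "to compare changes in the three quantitative variables" between the groups, "across three time points (before the intervention, immediately after the intervention, and 1 month later"), and for this "repeated measures analysis of covariance (ANCOVA) will be used, controlling for covariates". The covariates are not listed. The Abstract repeats the plan. Additional analyses {20b} adds only that suitable methods and adjusted analyses will be used. No section says which term or contrast of the model decides the primary outcome.

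**The concern.** The declared endpoint is a single between-group difference at one visit, chosen to show that the effect lasts. The stated analysis is a comparison of whole profiles in which the pre-intervention score is one of the response levels. Read in the ordinary way, a comparison of changes across three visits is the group-by-time interaction on 2 degrees of freedom. That test rejects when the arms diverge at any visit, including a divergence that has gone by 1 month.

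Two things are at stake. A significant result could be reported as success on the primary outcome when the lasting effect it is meant to show is absent. And because no deciding contrast is fixed, the choice among the interaction, the group effect and a 1-month comparison stays open until the results are seen. That matters more in an open-label trial (Who will be blinded {17a}).

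**Working it through.** **Inputs.** From Sample size {14}: SD 6, difference 4, two-sided alpha 0.05, power 80%, 36 per arm before dropout. From Outcomes {12} and {20a}: three visits, with 1 month as the primary one. Assumed, because the protocol gives no figure: the same SD at every visit and an equal correlation r between visits, taken as 0.3, 0.5, 0.6 and 0.7.

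**The plan's own figure.** n = 2 × 36 × (0.84 + 1.96)² / 16 = 35.28, so 36 per arm and 72 in total; 72 / 0.9 = 80. This reproduces. A plain t-test at one visit with 36 per arm has 79.7% power for 4 points.

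**Group-by-time test.** Let d be the three between-group differences (baseline, immediate, 1 month). The noncentrality is λ = (n/2) × Σ(d − mean d)² / [SD² × (1 − r)], referred to F on 2 and 140 df (critical value 3.06).

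- Transient effect, d = (0, 4, 0): mean 1.33; sum of squares 1.78 + 7.11 + 1.78 = 10.67.
- Sustained effect, d = (0, 4, 4): mean 2.67; sum of squares 7.11 + 1.78 + 1.78 = 10.67.

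The two sums are equal, so in both cases λ = 18 × 10.67 / [36 × (1 − r)] = 5.33 / (1 − r). Under equal correlation the test cannot tell a lasting effect from one that has vanished by the primary visit.

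**Group main effect** for d = (0, 4, 4). The estimated difference is (0 + 4 + 4)/3 = 2.67, the SD of a patient's three-visit mean is 6 × √[(1 + 2r)/3], and there are 70 df.

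**ANCOVA at 1 month on baseline PDQ-8.** The difference is 4, the residual SD is 6 × √(1 − r²), and there are 69 df.

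For both t-type tests the noncentrality is difference / (SD × √(2/36)).

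| Quantity | r = 0.3 | 0.5 | 0.6 | 0.7 |
|---|---|---|---|---|
| λ, group-by-time | 7.62 | 10.67 | 13.33 | 17.78 |
| Group-by-time rejects, effect (0, 4, 0) | 68.5% | 83.3% | 90.9% | 97.0% |
| 1-month test rejects, effect (0, 4, 0) | 5% | 5% | 5% | 5% |
| Group-by-time power, effect (0, 4, 4) | 68.5% | 83.3% | 90.9% | 97.0% |
| SD of three-visit mean | 4.38 | 4.90 | 5.14 | 5.37 |
| Group main effect power, (0, 4, 4) | 72.1% | 62.5% | 58.4% | 54.7% |
| ANCOVA residual SD | 5.72 | 5.20 | 4.80 | 4.28 |
| 1-month ANCOVA power, 4 points | 83.2% | 89.6% | 93.6% | 97.4% |

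**The case against.** The strongest reply is that {20a} names a model and no decision rule. It mentions no omnibus F test, no degrees of freedom and no criterion for success. A 1-month contrast can be taken from the same model, and which term is primary is often left to an analysis plan, which is not shown here. Much of this stands, and it limits the point in five ways.

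- A reader might infer that the stated model cannot test the 1-month endpoint or cannot give an estimate with a confidence interval. The text does not support that; the contrast is obtainable but not specified.
- A reader might infer that the trial loses power. That is not general. The interaction has the same 68.5 to 97.0% power for a sustained effect and exceeds 80% from r = 0.5 upward. The fall to 72.1/62.5/58.4/54.7% needs the group main effect to be the deciding term, and a comparison of changes does not suggest that reading.
- Keeping baseline as a response level is not an error in itself. Constrained longitudinal models do so and still estimate the 1-month difference validly. The unnamed covariates also do not rule out baseline adjustment.
- The link between the sample size and the 1-month visit is inferred. Section {14} speaks of quality of life and of sizing "to detect a difference of 4 units", without a visit.
- The correlations are assumed, and an effect of 4 that falls to exactly 0 is a worst case, not something the protocol expects.

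What the reply does not remove is that the section does state an analysis for the primary outcome, identical for all three scales, and its natural reading answers a different question from the one in {12}. Adding detail to a three-visit comparison of changes does not turn it into a 1-month test; someone has to name that contrast.

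**Conclusion.** The point holds as a mismatch of target. The primary outcome is PDQ-8 at 1 month, the stated analysis compares changes over three visits, and nothing names the 1-month between-group contrast as the primary test. If the group-by-time test decided the outcome, it would be significant in 68.5 to 97.0% of trials with an immediate 4-point effect and none at 1 month, against 5% for a test at that visit. This rests on the protocol's SD of 6 and 36 per arm, and on assumed equal variances and correlations of 0.3 to 0.7. The sample size arithmetic is correct. The documents do not show that the interaction will in fact be the deciding test, nor that the design is underpowered in general. The contrast should be fixed before any outcome data are analysed.

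**What to change.** State in {20a} that the single primary test is the between-group difference in PDQ-8 at 1 month, adjusted for baseline PDQ-8 and reported with its 95% CI. Obtain it either by ANCOVA at 1 month or as the 1-month contrast of a repeated-measures or mixed model. List the three-time-point analysis, the immediate post-intervention contrast, PFS-16 and GSE-17 as secondary. In {14}, add that the 4-unit difference refers to the 1-month visit, if that is what was meant.

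The cost is one paragraph. The number of patients, the data and the software do not change, and the baseline-adjusted test keeps power above 80% for a 4-point effect at every correlation examined.

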### Interim analyses {21b}

There will be no interim analyses conducted for this educational and care-based study, as it is considered low-risk. Since there are no safety concerns or critical endpoints that would require early stopping, the study will proceed according to the established protocol. Therefore, no stopping guidelines are applicable.

### Methods for additional analyses (e.g., subgroup analyses) {20b}

This study includes both an intervention group and a control group. The primary and secondary outcomes will be analyzed by comparing these two groups using appropriate statistical methods. Subgroup analyses may be conducted based on characteristics such as age, gender, or baseline health status to explore any differential effects of the intervention. Adjusted analyses will be performed to control for potential confounding variables.

### Methods in analysis to handle protocol non-adherence and any statistical methods to handle missing data {20c}

Participants who fail to attend more than two sessions, do not actively cooperate, or do not complete the required questionnaires will be considered non-adherent to the protocol. Initially, they will be reminded to complete the questionnaires or attend the sessions. If they continue to not comply, they will be excluded from the analysis. For missing data, any participants with incomplete data will be excluded from the final analysis.

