### Eligibility criteria {10}

#### Inclusion criteria

Patients eligible for participation in the study must meet the following criteria:Confirmed diagnosis: diagnosis of PD confirmed by a qualified neurologist specialized in movement disorders, based on the UK PD Society Brain Bank criteria [17].Willingness to participate: patients must express willingness to take part in the study [13, 36].Cognitive function: absence of cognitive impairment, confirmed by a neurologist’s evaluation [9, 37].Physical health: no severe physical illnesses that would prevent participation [38].Mental health: no acute or chronic psychiatric disorders [37].Neurological health: no history of acute or chronic neurological disorders, such as stroke or traumatic brain injury [37].Sensory abilities: no hearing or vision impairments that hinder participation [36].Literacy: ability to read and write [39].Medication use: no current use of psychiatric medications [39].Language: native Persian speakers.Family involvement: at least one family member must attend educational sessions alongside the patient.No concurrent interventions: patients must not participate in any other educational sessions or treatment-care interventions related to PD during the study period.

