#### Exclusion criteria

Patients will be excluded from the study if they meet any of the following conditions:Hospitalization: need for hospital admission during the study period.Absenteeism: absence from more than two sessions [39].Lack of cooperation: failure to actively participate or express unwillingness to continue [39].Cognitive decline: development of cognitive impairments during the study [9].

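### Randomised patients are removed, left unfollowed and dropped for post-randomisation events, partly by rules that only the intervention arm can fail, so the comparison is not as randomised and is likely, though not certain, to be biased towards the intervention

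*Protocol article*

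**What the plan says.** Under Intervention description {11a}, randomisation comes after consent and baseline questionnaires. Three later rules then decide who contributes outcome data.

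- **Exclusion criteria {10}.** The four items listed act during the study: "need for hospital admission during the study period", "absence from more than two sessions", lack of cooperation or unwillingness to continue, and new cognitive impairment.
- **Retention and follow-up {18b}.** "Participants who discontinue the intervention or deviate from the protocol will not be followed for outcome data". The only exception is supplying results or educational materials on request, and even then no further data are collected for analysis.
- **Non-adherence and missing data {20c}.** The definition reads: "Participants who fail to attend more than two sessions, do not actively cooperate, or do not complete the required questionnaires will be considered non-adherent". They are first reminded; then "If they continue to not comply, they will be excluded from the analysis". Separately, "any participants with incomplete data will be excluded from the final analysis".

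The sessions and calls in {11a} and Table 1 are for the intervention group. The control group receives routine care only. The trial is an open-label superiority trial ({8}, {17a}), and its primary outcome is PDQ-8 at 1 month ({12}), where higher is worse ({18a}).

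**The concern.** Randomisation protects the comparison only if patients are analysed in the arm assigned, whatever happens afterwards. Here the analysis set is defined by events after allocation, and some of those events can happen in one arm only. A control patient has no session to miss and no intervention to discontinue. An intervention patient who stops attending is removed, while a similar control patient stays. If those who stop are sicker or less motivated, the retained intervention group looks better on PDQ-8 without any treatment effect.

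Two features make this worse. First, {18b} means that the outcomes of such patients are never collected, so no later analysis plan can restore them. Second, the incomplete-data rule removes whole patients: someone who misses the immediate post-intervention questionnaire but supplies the primary 1-month PDQ-8 is still discarded.

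**Working it through.** **1. Which arm each rule can reach**

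| Rule | Section | Intervention | Control |
|---|---|---|---|
| Absence from more than two sessions | {10}, {20c} | yes | no sessions to miss |
| Discontinuing the intervention | {18b} | yes | nothing to discontinue |
| Hospital admission, cognitive decline | {10} | yes | yes |
| Lack of cooperation, unwillingness, deviation | {10}, {18b}, {20c} | yes | yes |
| Incomplete questionnaires | {20c} | yes | yes |

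The first two rows are one-sided by construction. No as-randomised analysis, imputation or sensitivity analysis appears elsewhere in the protocol to offset them.

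**2. The plan's own figure**

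Inputs from {14}: SD 6, difference 4, two-sided alpha 0.05, power 80%, dropout 10%.

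n = 2 × 6² × (0.84 + 1.96)² / 4² = 35.28, so 36 per group and 72 in total; 72 / 0.90 = 80. The stated 36, 72 and 80 are reproduced. The allowance replaces lost numbers; it does not keep the arms comparable.

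**3. Illustration of the bias**

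Assumptions, none given in the documents: true effect zero; SD 6; a share p of the 40 intervention patients removed and no control patient removed; those removed are g points worse on PDQ-8 than those kept; no covariate adjustment.

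- Bias = p × g, in favour of the intervention
- SE = 6 × √(1/(40(1−p)) + 1/40)
- False-positive rate = Φ(−1.96 + bias/SE) + Φ(−1.96 − bias/SE)

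SE is 1.378, 1.400 and 1.423 for p = 10%, 15% and 20%.

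| g (points) | p = 10% | p = 15% | p = 20% |
|---|---|---|---|
| 0 | bias 0; 5% | bias 0; 5% | bias 0; 5% |
| 3 | 0.30; 5.5% | 0.45; 6.2% | 0.60; 7.1% |
| 6 | 0.60; 7.2% | 0.90; 9.9% | 1.20; 13.5% |

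Worked cell, p = 20% and g = 6: bias 0.20 × 6 = 1.20; 1.20 / 1.423 = 0.843; Φ(−1.117) + Φ(−2.803) = 0.132 + 0.003 = 0.135. Against the 4-point target, 1.2 points is 30%.

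**4. Cross-check by simulation**

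Removal was linked to the PDQ-8 score through a latent variable with correlation ρ (20,000 runs, 40 per arm randomised, pooled t-test). With 10% removed and ρ = 0.3, the bias is 0.35 points and the false-positive rate 5.7%. With 20% removed and ρ = 0.5, they are 1.05 points and 11.5%. With ρ = 0 there is no bias. With 20% removed and ρ = −0.3 the bias is 0.63 points against the intervention.

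**The case against.** The best defence is that few patients may be removed. The trigger is absence from more than two sessions, not any missed session, and only after reminders and continued non-compliance ({20c}). Missed sessions are rescheduled ({11c}, {18b}), and questionnaires can be completed at the patient's home ({12}). This stands as a reason to expect a smaller loss, but the rule itself is unchanged.

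The direction is also open to challenge. The documents hold no data on who would be removed, and several rules reach both arms. A reader might infer that the result must favour the intervention; the text does not support that certainty. The planned covariate adjustment in {20a} could also absorb part of any selection on baseline severity. It cannot be relied on for selection by events after randomisation.

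Two further readings go beyond the documents:

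- **Serious loss of power.** With one-sided removal of 20% (32 against 40), t-test power for 4 points at SD 6 is 79.2%, against 79.7% for the planned 36 and 36. A fall to about 75% needs 32 in both arms, which is a different scenario. Absorbing dropout is also what the 10% allowance is for.
- **Removal when a relative does not attend.** The requirement that "at least one family member must attend educational sessions alongside the patient" is an inclusion criterion. No section removes a randomised patient for failing it.

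**Conclusion.** The concern holds in this form. Sections {10}, {18b} and {20c}, read together, remove randomised patients for post-randomisation events, leave those who discontinue or deviate unfollowed, and discard incomplete records. These are stated rules, not details left to an analysis plan, and part of them can act only on the intervention arm. That the comparison is not as randomised follows from the text alone. That the bias favours the intervention is likely but depends on who is removed.

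The size is not known from the documents. Under the assumptions shown, it runs from nothing to 1.2 PDQ-8 points, with a false-positive rate between 5% and 13.5%. The upper end needs 20% one-sided removal of patients a full SD worse than those kept. The point must be fixed even if the likely bias is modest, because uncollected outcomes cannot be recovered.

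**What to change.** - **{18b}:** continue to collect PDQ-8, PFS-16 and GSE-17 from every randomised patient who has not withdrawn consent to data collection, whatever their attendance and whether or not they stopped the sessions.
- **{20c}:** make the primary analysis all randomised patients in the arm assigned, using all available data through a likelihood-based mixed model for repeated measures or multiple imputation. Add a sensitivity analysis for data not missing at random. Keep the adherent, complete-data set only as a labelled supplementary analysis.
- **{10}:** state that the listed events do not remove a randomised patient from outcome follow-up or from the primary analysis, and reconcile {10}, {18b} and {20c}. This needs no rule on when the intervention should be stopped, and none is proposed here.

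The cost is protocol wording, a few extra questionnaire contacts (home completion is already provided for in {12}) and a possibly less favourable estimate. The follow-up change has to be in force before patients reach these events.
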